## Abstract

**Background:**

Despite the implementation of the preschool oral healthcare programme (POHP) for 5–6-year-old children over the past 3 decades in Malaysia, dental plaque and caries levels in this age group remain high. Among the child-level attributable factors are unhealthy self-care behaviours (poor oral hygiene and high sugary diet). In order to improve the children’s oral health, an improved programme called the ‘Senyuman Indah Milik Semua’ Programme (SIMSP) or ‘Beautiful Smile for All’ programme is introduced. In this programme, a triad of dental hygienist-teacher-parent works together to improve children’s oral hygiene levels compared with the existing POHP that involves dental hygienists only. The aim of this study is to compare the effect of the SIMSP versus the existing POHP on oral hygiene levels of 5–6-year-old children in the Kampar district, Perak state, Malaysia.

**Methods:**

This study is a pragmatic, cluster-randomised, parallel-group, matched pair, controlled trial with blinded outcome assessment. Randomisation is performed using a computer-generated table with a 1:1 allocation comparing the SIMSP and the POHP involving 28 preschools in the Kampar district, Perak, Malaysia. The intervention consists of preschool visits by a group of dental therapists, in-class oral health lessons and daily toothbrushing conducted by class teacher, child home toothbrushing supervised by parents, and infographic oral health messages to parents. The control consists of the existing POHP that involves preschool visits by a group of dental therapists only. The trial lasts for 6 months. Primary outcome variable is the mean plaque score change after 6 months. To determine the feasibility of the SIMSP, a process evaluation will be conducted using the perspectives of dental therapists, teachers, and parents on the appropriateness, effectiveness, facilitators, and barriers to the SIMSP implementation as well as an audit trail to assess the trial intervention.

**Discussion:**

Cluster randomisation may lead to a random effect and cluster selection bias. These factors will be accounted for when analysing the data and interpreting the outcomes. The effectiveness of the SIMSP will be evaluated by comparing the results with those of the POHP.

**Trial registration:**

ClinicalTrials.gov NCT04339647. Registered on 5 April 2020 – Retrospectively registered.

## Administrative information

The order of the items has been modified to group similar items (see http://www.equator-network.org/reporting-guidelines/spirit-2013-statement-defining-standard-protocol-items-for-clinical-trials/).

## Introduction

### Background and rationale {6a}

Oral disease is one of the costliest diet and lifestyle-related diseases [1]. Many oral health problems can be prevented and their early onset reversible. However, in some countries, there are a large number of children and parents who have limited knowledge on the causes and prevention of oral disease [2].

In Malaysia, preschool children are one of the target groups in the delivery of dental services by the Ministry of Health, Malaysia [3]. The preschool oral healthcare programme (POHP) was introduced in 1984 to provide preventive and curative treatment as well as oral health education (OHE) to preschool children aged 5–6 years [3]. The POHP is delivered by dental therapists (DTs) who visit preschools twice a year. In the first visit, DTs will conduct an oral examination followed by OHE using either role play, puppet show, video presentation, or tell-show-do technique. On the same visit, a toothbrushing exercise and a fluoride varnish application are carried out. The second visit takes place after 6 months where DTs will perform atraumatic restorative treatment [4] using glass ionomer restorations followed by a second application of fluoride varnish. Apart from preschool children, DTs also provide oral healthcare to primary and secondary school children, children with special needs, elderly people, and provide OHE to selected government agencies and health centres [5].

Although the POHP covers most preschools in Malaysia for the past 3 decades except private preschools, the prevalence of caries and children with dental plaque in this age group remain high. The national oral health data in 2005 showed that 76.2% (mean dft = 5.5) of 5-year-old children had caries in the primary teeth [6] and the prevalence reduced to 71.3% (mean dft = 4.8) after 10 years [7]. Both prevalences are well over the national target of 50% caries in this age group by 2020 [8]. In comparison, caries prevalence in this age group was slightly lower than the median caries prevalence of 79% among 5–6-year-old children in Southeast Asia in 2017 (mean dft = 5.1) [9]. The limitations of the current POHP in controlling caries and dental plaque in young children had been highlighted in the 2015 national oral health survey report [7]. Among the attributable factors highlighted were limited resources, lack of time, wider job scopes of DTs, and lack of parental and teachers’ involvement in children oral health. All these led to poor self-care behaviours of children.

In order to improve the POHP and to prevent preschool children from developing future caries in permanent dentition, positive changes in children’s self-care behaviours are crucial [10]. Positive changes in oral health behaviours would lead to long term reductions in dental plaque and dental caries. As children live with parents and attend school, positive changes in oral health behaviours in this age group would invariably require the combined efforts of DTs, parents and teachers in children’s oral health [11, 12].

Based on the 2015 survey findings, the recommendations put forward to improve the existing POHP are to strengthen the DT’s role in preschool oral health, empower parents, and include teachers in OHE. The use of social media in OHE is also recommended [13]. As the result, the Senyuman Indah Milik Semua Programme (SIMSP) or Beautiful Smile for All Programme was introduced in 2019 taking into account scientific evidence, best practice, and stakeholders’ feedback. In addition to the DT’s role in current POHP, the SIMSP will also include active participation of teachers and parents. The details of the SIMSP are described in the “Methods: participants, interventions, and outcomes” section.

### Scientific hypothesis

The scientific hypothesis of the study is that the SIMSP is more effective than the POHP to improve preschool children’s oral hygiene after 6 months. If it is proven effective, the SIMSP may be absorbed into the current oral healthcare service to replace the POHP.

### Objectives {7}

The primary objective of the study is to assess the effect of the SIMSP versus existing POHP on mean plaque score change among 5–6-year-old children over 6 months.

The secondary objectives are:

1) To assess the impact of the SIMSP versus existing POHP over 6 months in terms of:
Changes in children’s oral health behavioursMean change in parental oral health literacy (OHL) score

2) To undertake a process evaluation using the perspectives of DTs, teachers, and parents on the appropriateness, effectiveness, facilitators, and barriers to the implementation of the SIMSP intervention.

#### Hypothesis (alternative)

The SIMSP is effective to reduce plaque scores among 5–6-year-old children compared to existing POHP.The SIMSP is effective to promote positive changes in oral health behaviours among 5–6-year-old children compared to existing POHP.The SIMSP is effective to improve parental OHL scores compared to existing POHP.

### Trial design {8}

The study design is a pragmatic, cluster-randomised, parallel-group, matched pair, controlled trial with blinded outcome assessment.

## Methods: participants, interventions, and outcomes

### Study setting {9}

The trial will be centred at government-funded preschools in Kampar district, Perak state, Malaysia. There are 53 preschools altogether, and the preschools are paired according to geographical location and preschool characteristics into 24 pairs (5 preschools are not paired as their locations are far away from each other).

### Eligibility criteria {10}

The inclusion criteria for preschool are government-funded preschool that receives the POHP. The inclusion criteria for children are healthy children aged 5–6 years, understand Malay language, live with parents/caregivers, and have a written informed consent. For parents/caregivers, they must be fluent in Malay language and live with the child.

Children with chronic medical conditions, dental/oral developmental conditions, physical disability or long term medication are excluded.

### Who will take informed consent? {26a}

DTs will inform parents about the study in a letter to be sent through school teacher. The letter contains information sheets about the study and a consent form. A contact telephone number is included in the consent form for parents to call the DTs if they have any questions about the study. A written informed consent from parents will be obtained before their child can be included in the study.

### Additional consent provisions for collection and use of participant data and biological specimens {26b}

A verbal consent from children will be obtained before their teeth are examined.

### Interventions

#### Explanation for the choice of comparators {6b}

Preschool children in the control group will receive the existing POHP provided by the Oral Health Programme, Ministry of Health. In the POHP, a team of DTs will visit the preschool twice/year. The activities will consist of an oral examination, OHE including toothbrushing exercise, fluoride varnish application twice/year, and simple treatment using glass ionomer restorations (if required).

#### Intervention description {11a}

The SIMSP was developed based on feedback from experts in dental public health discipline, senior dental officers in the Ministry of Health, preschool curriculum experts in the Ministry of Education, preschool teachers, a child psychologist, and parents. The concept of the SIMSP is that improvement in preschool children’s oral hygiene would require the combined efforts of DTs, preschool teachers, and parents working together on children’s oral health. The SIMSP’s target groups are preschool children and their parents. It consists of the following package:

1) Preschool children:
Oral examination, OHE, fluoride varnish application twice/year, and simple treatment by DTs (usual care/POHP);In-class oral health lessons by teacher based on the teacher’s OHE booklet over a period of 6 months;In-school daily toothbrushing with fluoride toothpaste (1450 ppm fluoride) supervised by class teacher for 6 months;Supervised home toothbrushing at night by parents/guardians.

2) Parents/guardians:
Attend a parent-DT meeting at school to discuss on child’s caries risk assessment (CRA);Received OHE and diet advice from DT based on child’s CRA levels (low/medium/high);Received free toothbrush and fluoride toothpaste (1450 ppm fluoride) for child home toothbrushing;Received 10, 2-weekly oral health infographics from DT sent via electronic messaging application (WhatsApp) for a duration of 5 months (printed versions for parents without a smartphone).

#### Teacher’s OHE booklet

The OHE booklet was developed prior to the study for use by teachers as a teaching tool for in-class oral health lessons. The content was developed by experts in dental public health discipline based on thorough review of dental literature. It consists of 6 oral health domains with 11 topics. The first domain covers basic knowledge about teeth with 4 topics: (i) your teeth, (ii) healthy teeth and their use, (iii) milk and permanent teeth, and (iv) why my teeth are loose? The second domain covers basic knowledge on toothbrushing with 1 topic: Toothbrushing is fun. The third and fourth domains promote children’s awareness on oral disease with 2 topics: (i) dental caries and (ii) gum disease, respectively. The fifth domain provides awareness on sugary diet with 1 topic: Sugars are bad for teeth. The sixth domain teaches about self-motivation with 3 topics: (i) you can do it, (ii) going to the dentist, and (iii) beautiful smile for all.

The OHE booklet was content validated by a paediatric dentist, a periodontist, and a general dentist. The delivery method and the level of language used were assessed and verified by a child psychologist. Subsequently, preschool teachers’ feedback was sought on the overall appearance of the booklet and the suitability of the worksheets for preschool children use. The booklet was tested on a group of preschool children who were not involved in the main study to assess its utility as a teaching tool before it was finalised. It was subsequently endorsed by the Committee on Preschool Curriculum from the Ministry of Education who were experts in preschool pedagogy and assessment before being used in the study. Teachers in the SIMSP will deliver oral health lessons based on the OHE booklet every 2 weeks for 6 months. Each lesson will take approximately 20 to 30 min. At the end of each lesson, a revision in the form of a colouring worksheet will be distributed to the children as part of the learning activities.

#### Parent's oral health infographics

The parents/caregivers’ oral health infographics were developed prior to the study. The infographics consist of 5 domains with 10 topics related to oral health. The content was developed by experts in dental public health discipline and validated by a paediatric dentist, a periodontist, and a social media expert. The first domain has 1 topic on knowledge of teeth structure and eruption dates. The second domain relates to oral health habits with 2 topics: (i) good oral health habits and parental roles in children’s oral health, and (ii) poor oral health habits. The third domain covers knowledge on oral disease with 2 topics: (i) dental caries, and (ii) periodontal disease. The fourth domain relates to toothbrushing with fluoride toothpaste with 2 topics: (i) toothbrushing, and (ii) use of fluoride toothpaste. The fifth domain contains information on dental treatment and prevention with 3 topics: (i) fluoride varnish, (ii) fissure sealant, and (iii) treatment of oral disease. The infographics were tested with a group of preschool parents. Their opinions for improvement were sought before the infographics were finalised. In the SIMSP intervention, the infographics will be sent to parents/guardians every 2 weeks over a period of 5 months.

#### Caries risk assessment (CRA) form

The CRA form used in this study was adapted from the CRA template developed by experts during the Malaysia Early Caries Expert Workshop 2014. It consists of 4 parts taking into account the clinical, environmental, behavioural, and factors associated with parents/caregivers [14]. Part 1 contains information on child’s caries experience assessed by DTs using the International Caries Detection and Assessment System (ICDAS) [15]; part 2 contains information on caries risk factors of the child: presence of visible plaque, use of fluoride toothpaste, presence of crowding/deep fissures, consumption of sugary snacks, bottle feeding at night, and mother/siblings with caries (visible plaque and crowding/deep fissures were assessed together in Part 1); part 3 contains information on the caries risk indicator of the child, i.e. low, medium, or high based on information in parts 1 and 2; part 4 contains information on caries management of the child including individual treatment plan, and tailored OHE and dietary advice given to parents during parent-DT meeting.

### Control

Preschool children in the control group received the usual care/POHP delivered by DTs in 2 visits/year. It consists of an oral examination, OHE (including toothbrushing exercise), fluoride varnish application twice/year, and simple treatment.

### Implementation of the intervention

The SIMSP intervention is delivered for a period of 6 months (Fig. 1). It consists of 3 phases:

**Fig. 1 Fig1:**
[figure not shown]
Timeline of the study

#### Phase 1: DT first visit to preschools in both groups

A written informed consent from parents for their children’s involvement in trial will be sought when the preschools open in the new academic year. The first visit of DTs to preschools occurs in the beginning of the year to conduct an oral examination of the children for caries and dental plaque. In the SIMSP group, the presence of crowding/deep fissures on the teeth will be charted and this information will be included in the CRA form. A self-administered questionnaire for parents will be sent through class teacher.

#### Phase 2: DT second visit to preschools and initiation of intervention

This visit takes place 2 weeks after the first visit. In the SIMSP group, DTs will deliver a standardised OHE to children followed by a fluoride varnish (20,000 ppm fluoride) application on their teeth. At this visit, DTs will meet parents to discuss their child’s oral health status and fill in the child’s CRA form. Parents are given OHE and dietary advice based on their child’s caries risk levels (low/medium/high). A set of free toothbrush and fluoride toothpaste (1450 ppm fluoride) is given to parents for child home toothbrushing along with instructions. Parental agreement to receive 10 oral health infographics via WhatsApp every 2 weeks for the next 5 months will be sought. With regards to teachers, they will receive the Teacher OHE booklet to be used as a teaching aid for teaching oral health lessons in class. Teachers will also be given enough supplies of toothbrush and fluoride toothpaste for children’s daily toothbrushing over 6 months. Teachers are given instructions on toothbrushing and a teeth model to help them with the activity. In the control group, DTs will deliver the POHP that consists of a standardised OHE (including toothbrushing exercise) followed by a fluoride varnish (20,000 ppm fluoride) application on children’s teeth.

#### Phase 3: DT third visit to preschools

This visit will take place 24 weeks after the second visit. In this visit, DTs will perform simple dental treatment on the children (if required) followed by the second application of fluoride varnish (20,000 ppm fluoride). Children in the SIMSP and POHP groups will receive the same treatment on the third visit.

### Criteria for discontinuing or modifying allocated interventions {11b}

This section is not relevant as children in both groups will not receive any drug prescriptions except fluoridated toothpaste and fluoride varnish application.

### Strategies to improve adherence to interventions {11c}

A face-to-face instructions to parents will take place during parent-DT meeting at the beginning of the year. This session will include:
Instructions on child home toothbrushing.The importance of reducing child’s daily sugar intake and practising healthy bottle-feeding pattern.

A reminder will also be sent via WhatsApp messaging platform every month.

For teachers, face-to-face adherence reminder sessions will take place at the beginning of the intervention at school and monthly for 6 months. This session will include:
Revision on the delivery of the OHE lessons in classRevision on children’s daily toothbrushing supervision at school.

Procedures for monitoring adherence will involve several other methods; in-class lessons by filling in the lesson dates in the booklet by teacher, in-school toothbrushing by completing a toothbrushing diary by teacher, parental meeting with DTs by completing the attendance list by DTs, and infographics sent to parents by completing a standardised report form by DTs. At the same time, feedback from teachers, DTs, and parents will be gathered by means of focus group discussion (FGD) (with parents and DTs) and in-depth interview (with parents) to assess the process implementation of the SIMSP intervention.

### Relevant concomitant care permitted or prohibited during the trial {11d}

The children are allowed to visit the dentist and receive treatment for any dental problems they face during the study period. Cases of non-adherence or deviation from the study protocol will be reported. Their data may not be included in the analysis.

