#### Methods for additional analyses (e.g. subgroup analyses) {20b}

No additional analyses will be conducted in the trial.

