#### Methods in analysis to handle protocol non-adherence and any statistical methods to handle missing data {20c}

Intention-to-treat analysis [15] will be carried out for the primary and secondary outcome measures in the study [20].

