##### Frequency and plans for auditing trial conduct {23}

The researchers will observe the implementation fidelity of the SIMSP to ensure that it is delivered as planned throughout the 6-month period. Data on implementation fidelity are collected by the researchers through various methods; in-class lessons by filling in the lesson dates in the booklet by teacher, in-school toothbrushing by completing a toothbrushing diary by teacher, parental meeting with DT by completing the attendance list by DTs, and infographics sent to parents by completing a standardised report form by DTs. At the same time, feedback from teachers and DTs by means of FGD and parents by means of in-depth interviews will be collected to assess the acceptability, feasibility (facilitators and barriers), effectiveness, and suggestions for improvement in implementing the SIMSP. The researchers will visit the preschools 3 times over the 6-month period to monitor the implementation fidelity at each preschool. Variations in the implementation process between preschools are minimised through discussion and support.

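### The protocol lets data from non-adherent or deviating cases be left out of the analysis, which contradicts its promise of intention-to-treat; adherence-based exclusions would fall mainly in the SIMSP arm.

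*Protocol article*

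**What the plan says.** Three statements in the protocol article bear on who is analysed.

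- Section {11d}, on concomitant care, first allows children to see a dentist outside the trial, then adds: "Cases of non-adherence or deviation from the study protocol will be reported. Their data may not be included in the analysis". It gives no criterion, names no one to decide, and does not say whether a case is a child, a class or a preschool. It is not limited to one arm.
- Section {20c}, on non-adherence and missing data: "Intention-to-treat analysis [15] will be carried out for the primary and secondary outcome measures in the study".
- Section {20b}: "No additional analyses will be conducted in the trial".

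Section {11c} describes how adherence is recorded. The teacher's part is "in-class lessons by filling in the lesson dates in the booklet by teacher, in-school toothbrushing by completing a toothbrushing diary by teacher". The part kept by the dental therapists is "parental meeting with DTs by completing the attendance list by DTs, and infographics sent to parents by completing a standardised report form by DTs". Section {23} lists the same four records as fidelity data and describes the audit in terms of one arm: "The researchers will observe the implementation fidelity of the SIMSP to ensure that it is delivered as planned throughout the 6-month period".

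**The concern.** Intention-to-treat means that adherence and deviation do not decide who is analysed. A rule under which they may decide it cannot stand beside that promise, and the analysis population for the primary outcome is left open.

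The article calls the trial pragmatic, and its hypothesis section says that SIMSP may replace POHP if it proves effective. That decision needs the effect of offering the programme, including to teachers and parents who take it up poorly. The Discussion expects such cases: it says that delivery depends on teachers' commitment and names parents' willingness to monitor brushing as a challenge. If these children were removed from SIMSP with no counterpart removed from POHP, a selected group would be compared with an unselected one, and the protection of randomisation would be lost.

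Timing adds to this. Under Trial status, the quantitative outcome data are already collected and cleaned and the multi-level analysis is under way. An exclusion rule without criteria would now be applied with outcomes in hand.

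**Working it through.** **1. Can the statements be reconciled?**

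| Reading of {11d} | Against {20c} and {20b} |
|---|---|
| 'May not' as a prohibition: such data are left out | Contradicts intention-to-treat outright |
| 'May not' as a permission: such data can be left out | Contradicts intention-to-treat whenever it is used; no criterion says when |
| {11d} describes a separate per-protocol analysis | Excluded by {20b}, which allows no additional analyses |

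No other section resolves the conflict.

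**2. Where would adherence-based exclusions fall?**

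| Record ({11c}, {23}) | Kept by | Component in POHP? |
|---|---|---|
| Lesson dates in the booklet | Teacher | No |
| Toothbrushing diary | Teacher | No |
| Parent-meeting attendance list | Dental therapist | No |
| Infographics report form | Dental therapist | No |

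The Control section describes dental therapist visits only, and no adherence record is described for that arm. Only the attendance list records what a parent did. The two teacher records would tend to identify a class or a preschool. An exclusion based on them could remove a whole cluster and break one of the 14 matched pairs.

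**3. The plan's own sample size.** Section {14} gives an effect size of 0.30, α = 0.05 and power 0.8. A two-sample t-test at two-sided 0.05 needs 175.4 per group, rounded up to 176, or 352 in total, as stated. Then (352 + 70.4) × 1.5 = 633.6, rounded to 634, also as stated. This point disputes neither figure.

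**4. Illustration of the bias.** These assumptions are not in the documents: no true effect of offering SIMSP; a fraction f of SIMSP children excluded; their plaque change g SD worse than that of the children kept; no POHP child excluded.

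Let a be the mean benefit among the children kept, in SD. With no true effect, (1 − f)a + f(a − g) = 0, so a = f × g. This is the spurious advantage.

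The effective total is 634/1.5 = 422.7, or 211.3 per arm before exclusions. SE = √[1/(211.3(1 − f)) + 1/211.3]. Two-sided type I error = P(Z > 1.96 − a/SE) + P(Z < −1.96 − a/SE).

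| f | g | a = f × g (SD) | Share of 0.30 | SE | a/SE | Type I error |
|---|---|---|---|---|---|---|
| 0.05 | 0.2 | 0.01 | 3% | 0.099 | 0.10 | 0.051 |
| 0.10 | 0.3 | 0.03 | 10% | 0.100 | 0.30 | 0.060 |
| 0.20 | 0.3 | 0.06 | 20% | 0.103 | 0.58 | 0.090 |
| 0.20 | 0.5 | 0.10 | 33% | 0.103 | 0.97 | 0.163 |
| 0.30 | 0.5 | 0.15 | 50% | 0.107 | 1.40 | 0.288 |

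These rows assume that all 634 children contribute outcomes. If the 20% allowance for non-response is used up, the effective size returns to 634/1.5/1.2, about 352 (176 per arm). The last two rows then give 0.143 and 0.248. The spurious advantage itself does not depend on sample size.

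**The case against.** A reader might infer that the plan tracks non-adherence in one arm in order to exclude, and that exclusions would certainly favour SIMSP. The documents do not support that. The rule in {11d} is neutral between arms. It follows directly on the sentence about outside dental visits, which can occur under POHP as well. No section links the four records to exclusion from analysis; {23} presents them as fidelity data. The direction is an inference. It needs exclusions to fall mainly in SIMSP and the excluded children to have worse plaque change. The first is likely given the records, and the second is plausible, but neither is documented.

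A reader might also take one scenario, such as 20% excluded and 0.5 SD worse, as the size of the bias. Neither figure is in the article, and at the low end of the range the effect is negligible.

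Finally, {20c} is the item that governs non-adherence, and 'may not' can be read as a permission that is never used. On that reading the analysis could still be by intention-to-treat. This softens the conflict but does not remove it, because the article does not say that {20c} prevails and sets no limit on using the permission.

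**Conclusion.** The contradiction between {11d} and {20c} stands, and {20b} closes the one reading that would reconcile them. It has to be resolved because it determines the primary analysis population. This part rests on the text alone.

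That the described adherence records are one-sided is also on the page. Bias towards SIMSP is an expectation and not a stated fact. Under the assumptions shown it ranges from 0.01 to 0.15 SD, or 3% to 50% of the planned 0.30 SD, with a type I error from about 0.05 to 0.29. The calculation treats exclusions as falling on individual children. Loss of whole classes or preschools, or of matched pairs, is not modelled.

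**What to change.** - In {11d}, keep the sentence on reporting non-adherence and deviations, and delete the one that follows it.
- State there or in {20c} that non-adherence, protocol deviation or outside dental treatment is not a ground for exclusion from the primary and secondary analyses. All consented children are analysed in the arm to which their preschool was allocated.
- If an adherence-restricted analysis is wanted, label it secondary, set criteria for both arms in advance (including whether they apply to a child, a class or a preschool), and amend {20b} to allow it.

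The cost is a few sentences. No new data are needed and the sample size does not change. Children without a 6-month plaque score are a missing-data question, which this change neither settles nor makes harder. As the analysis is already in progress, the wording should be settled before any exclusion is made and before results are released.
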